**The ‘Motivation to Exercise’ study**

**Principal Investigators:** [name], [name]

1. **Background and Significance/Relevance**

The Dietary Guidelines for Americans (DGA) provide science-based advice to promote health and to reduce risk for chronic diseases through diet and physical activity [[1](#_ENREF_1)]. However, advice alone is not effective for motivating behavior change; additional strategies are needed as only 1 in four Americans report engaging in any leisure time physical activity [[2](#_ENREF_2)], and only 9% meet the Physical Activity Guidelines for Americans [[3](#_ENREF_3)]. The low adherence of most Americans to physical activity recommendations underscores the need for research on factors affecting the adoption of two key aspects of the DGA: increased physical activity, and attainment of a healthy weight. This project addresses such factors and will yield empirical evidence that will inform physical activity guidelines and programs, as well as tools to help individuals make healthy choices regarding physical activity and maintenance of healthy body weight.

Behavioral Choice Theory provides a framework for understanding the choices people make and how to shift an individual’s choice toward healthier alternatives. The theory holds that choice is based on the relative motivating values of alternatives. One way to shift choice toward a healthier alternative is to increase the relative reinforcing value (RRV)/motivating value of that alternative. Thus, increasing the RRV of PA behaviors could shift choice towards PA and away from less healthy, sedentary alternatives. Physical activity has reinforcing properties in that exercise dependency has been demonstrated in both humans [[4-7](#_ENREF_4)] and rodents [[7-10](#_ENREF_7)]. Moreover, wheel-running in rodents produces a reinforcing aftereffect, which can be measured by conditioned place preference after the activity has ceased [[10](#_ENREF_10)]. Although human data are limited, individual differences in the RRV of physical activity (RRV_PA_) [[11-15](#_ENREF_11)] have been reported, which predict total usual PA [[16](#_ENREF_16)]. We have shown that RRV_PA_ is associated with greater health-promoting, moderate-to-vigorous intensity PA [[11](#_ENREF_11)].

Increasing the RRV_PA_ may allow PA to compete with more reinforcing, sedentary behaviors, resulting in a shift in behavioral choice. This process is termed “incentive sensitization”, which was originally proposed to explain drug addiction [[17](#_ENREF_17)]. Incentive Sensitization theory posits that the RRV of a behavior is increased through repeated exposures, which produce neuroadaptations that increase craving of the behavior [[18](#_ENREF_18)]. After repeated exposures to a stimulus, a ‘sensitization’ or hypersensitivity to the incentive motivational effects of the stimulus follows. This produces a bias of attentional processing towards the stimuli (i.e., increases its salience within the environment; incentive salience) [[19](#_ENREF_19), [20](#_ENREF_20)]. The result is an increased RRV of the stimulus relative to a competing alternative. The extent to which the RRV_PA_ can be increased has not been studied. Understanding the conditions that produce incentive sensitization for PA and the individual difference factors that may moderate the incentive sensitization process would yield a wealth of new information that could be used to help individuals make healthy choices and increase adherence to the DGA.

Another factor that influences motivation for a behavior is the development of tolerance to unpleasant aspects of that behavior. Opponent-Process Theory would account for the acquisition of motives such as use of drugs of abuse where the initial reinforcer is positive, and PA where the initial reinforcer may be negative [[21](#_ENREF_21)]. Solomon [[21](#_ENREF_21)] showed that the former case increases the affective state (State A, the rush) up to the point at which the effect of the drug wanes, resulting in an aversive-affective state characterized by craving (State B, withdrawal). Over time, State B also decays and there is a return to baseline. However, after frequent self-administrations, tolerance is developed and the positive reinforcing state (A) is greatly diminished in both intensity and duration, while the acquired motivational state (B) is heightened in both intensity and duration. Thus, both the onset of State A and the removal of the aversive State B serve to motivate behavior [[21](#_ENREF_21)].

The opposite is proposed when the initial reinforcer is negative, as may be the case for exercise. For initial exposures, the thought of exercise can produces anxiety followed by discomfort and sweating during the exercise session (State A). This is followed by relief (State B) before the ultimate return to the resting state. It is possible, however, that after many repeated exposures, tolerance may develop to the aversive aspects such that anxiety is replaced with eagerness and there is excitement and pleasure during exercise, leading to the after-reaction in State B of exhilaration followed by a gradual return to a resting state. Opponent Process Theory predicts that the affect experienced after repeated exposures is opposite to that experienced during the first few presentations [[21](#_ENREF_21)]. For exercise, this would include tolerance to any discomfort, pain, fatigue and displeasure and a greater positive post-exercise affective response [[22](#_ENREF_22)]. This is important, as the affect experienced during and after exercise is known to have a greater motivational significance in PA participation than knowledge and beliefs regarding health benefits[[22](#_ENREF_22)]. Therefore, we propose that repeated exposures to PA will produce tolerance to any unpleasant aspects while increasing the post-exercise affect [[23](#_ENREF_23), [24](#_ENREF_24)].

Sensitizing PA reinforcement and increasing discomfort tolerance may be associated with the duration and intensity of daily activity bouts [[6](#_ENREF_6), [25-28](#_ENREF_25)]. We anticipate that a moderate PA dose (300 kcal expenditure) will produce greater incentive sensitization and tolerance than a low dose (150 kcal). This is based on observations that the development of sensitization of drugs of abuse is dose-dependent, with mid-range doses increasing reinforcement more than either low or very high doses [[29](#_ENREF_29)].

This study will address the primary question of:

- Can repeated exposure to PA increase the RRV_PA_ in sedentary individuals?

This study will address the secondary/exploratory questions of:

- Can repeated exposure to PA increase tolerance to aversive aspects of PA?
- Is increased RRV_PA_ associated with increased usual PA?
- Is increased discomfort tolerance associated with increased usual PA?

1. **Hypotheses to be Tested**

**Primary hypothesis**

*Hypothesis 1:* 300 kcal doses of PA will increase RRV_PA_ more than 150 kcal doses and no PA.

**Secondary/Exploratory hypotheses**

*Hypothesis 2:* 300 kcal doses of PA will produce greater exercise discomfort tolerance than 150 kcal doses and no PA.

*Hypothesis 3:* Increases in the RRV_PA_ will be positively associated with the change in usual PA.

*Hypothesis 4:* Increases in discomfort tolerance will be positively associated with the change in usual PA.

| Table 1. Design of experiment | | | | | |
| --- | --- | --- | --- | --- | --- |
| Sex | PA dose | 0 wk | 6 wk | | 10 wk |
|  |  | <-treatment-> | |  |  |
| Male | 0 kcal (n=15) | X | X | | X |
|  | 150 kcal (n=15) | X | X | | X |
|  | 300 kcal (n=15) | X | X | | X |
|  |  |  |  | |  |
| Female | 0 kcal (n=15) | X | X | | X |
|  | 150 kcal (n=15) | X | X | | X |
|  | 300 kcal (n=15) | X | X | | X |

**C. Methods**

**i. Participants and screening**: As shown in Table 1, 45 men and 45 women age 18-49 y, that range in adiposity from lean to obese (19-35 kg/m^2^) and have no contraindications for PA participation will be recruited. Subjects will be sedentary, i.e. not be regularly engaging in exercise more than once per week. They will be instructed to not enroll in an exercise program and to limit planned PA to that prescribed by the investigators for the duration of the incentive sensitization treatment. Subjects cannot have high occupational activity such as construction trades, farm workers, and freight movers who complete most of their work by hand. Additional exclusionary criteria include a liking of <3 out of 10 for all available PA modes and exercising for more than 30 min/day > 2d/wk and repeated non-compliance with completing the exercise sessions. Participants will be screened for entry criteria and will report the times/wk they engage in various types of PA.

**ii. Design:** Physical activity will be performed on stationary cardio-type exercise machines (choice each day of treadmill, elliptical, stair stepper, cycle). Each treatment will be 6 wk in duration with 3 treatment sessions/wk. Outcome testing will occur at baseline, 3, 6, 10, and 14 wks. As shown in **Table**

**1**, participants will be randomized to exposures of 0, 150, or 300 kcal/session. The 150 kcal and 300 kcal dose groups will participate in 3 physical activity sessions (days)/wk. All participants will be provided Choice Health and Fitness (CHF) memberships, the 0 kcal dose group will receive their CHF membership and exercise program after they complete the study.

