**iii. Procedures**:

Visit One: Screening and Consent

Participants will be recruited by Grand Forks Human Nutrition Research Center (GFHNRC) staff using Survey Monkey. We will leverage our partnership with Choice Health and Fitness to utilize their electronic entry records and send recruitment materials to those fitness club members who attend Choice Fitness 2 or fewer visits per week and otherwise seem to meet our other entry criteria. Various other media will be used to advertise the study. This may include brochures, print media such as the Grand Forks Herald, Dakota Student, Exponent, and Tidbits, television and radio such as the UND television and radio stations. Internet advertisements including University Research Newsletter, University Letter, HEALTHY-UND Listserv, and Work Well Newsletter may be utilized. Recruitment efforts may also include posting flyers around the Greater Grand Forks area and surrounding communities, promoting the study at expos and trade shows, and providing information on the GFHNRC website. Recruitment will continue until the study needs are met. A sample advertisement is attached (APPENDIX 1 a/b). Subjects may apply to join the study by completing the on-line application on Survey Monkey (APPENDIX 2). Eligible applicants will be invited to an information/screening appointment at the GFHNRC or CHF. During this initial visit, subjects will be informed about the study and have any questions answered. If deemed eligible and the subject desire to participate, they will be asked to provide written informed consent (APPENDIX 3). After signing the consent, subjects will fill out a demographic form (APPENDIX 4), a medical history form (APPENDIX 5), and be measured for anthropometrics. Subjects will also be provided a SenseWear device to wear for the following week to monitor free-living energy expenditure and physical activity. Questionnaires including The Preference for and Tolerance of the Intensity of Exercise Questionnaire (PRETIE-Q) (Appendix 6) [[30](#_ENREF_30), [31](#_ENREF_31)], the Discomfort Intolerance Scale [[32](#_ENREF_32)] (Appendix 7), Social norms [[33](#_ENREF_33)], Social Support and Exercise Survey (APPENDIX 8) [[34](#_ENREF_34)], the Exercise Self-Efficacy Scale (EXSE, Appendix 9) [[35](#_ENREF_35)] and the Exercise Confidence Survey (APPENDIX 10), Psychological needs satisfaction (PNSE) (APPENDIX 11), and the Behavioral Regulation in Exercise questionnaire (BREQ-3) (APPENDIX 12) will be completed by the subject at this time. The first of four dietary recalls will be completed and the subject will be scheduled for their three baseline visits at (CHF).

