6-Week Intervention The treatment is based on meeting the prescribed kcal expenditure as measured using the SenseWear device (described below) three times per week. The intensity, duration, and interval/ constant load nature of physical activity will not be prescribed. For approximately the first six sessions, a research assistant will be present to provide instruction on the use of the stationary exercise machines and will monitor each session for attaining the energy expenditure goal of either 150 kcal or 300 kcal. The study-related exercise will be a circumscribed and intentional bout recorded by the participant in a log book. Compliance regarding the energy expenditure of each physical activity session will be monitored by the subject and staff using an activity monitor. A research assistant will meet with the subject each week at the fitness center to download and review the activity monitor wear log (APPENDIX 20) and activity monitor data with the volunteer. Volunteers will be given feedback if the exercise bout cannot be readily identified from the activity monitor or if the bout did not meet the energy expenditure criteria. To promote external validity and minimize seasonal/weather effects, treatment sessions will occur at the fitness center. Subjects in the 0 kcal group will wear the physical activity monitor only during assessment periods. No instruction will be provided regarding dietary intake as spontaneous change in dietary intake is an outcome measure.

Week-6 Assessments (Post)

At the conclusion of the intervention, participants will follow the testing schedule outlined for the baseline assessments. Additionally, the Perceived Autonomy support questionnaire will be administered (APPENDIX 21) and subjects will be issued an activity monitor to wear for the following week and will return to CHF to return the device.

Week 10 Assessments

After four weeks of no-contact with the study investigators, subjects will follow the testing schedule outlined for the baseline assessments except they will not complete a body composition test. Subjects will be issued an activity monitor to wear for the following week and will return to CHF to return the device.

**iv. Measures**: Gender, baseline age, and baseline values of outcomes will be tested as moderators of change in RRV of physical activity (**Table 2**).

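### Exclusion for repeated non-compliance with exercise sessions acts after randomisation and only in the two exercise arms, so it can be expected to bias exercise v 0 kcal

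*Protocol*

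**What the plan says.** The exclusion criteria in C. Methods, i. Participants and screening, end with "exercising for more than 30 min/day > 2d/wk and repeated non-compliance with completing the exercise sessions". No number of missed sessions is given, and no consequence for follow-up or analysis is stated.

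Under ii. Design, "participants will be randomized to exposures of 0, 150, or 300 kcal/session". Only two of the three arms have sessions: "The 150 kcal and 300 kcal dose groups will participate in 3 physical activity sessions (days)/wk", whereas "the 0 kcal dose group will receive their CHF membership and exercise program after they complete the study".

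Under iii. Procedures (6-Week Intervention), compliance is judged session by session during treatment: "Compliance regarding the energy expenditure of each physical activity session will be monitored by the subject and staff using an activity monitor". For controls, "Subjects in the 0 kcal group will wear the physical activity monitor only during assessment periods".

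The primary hypothesis is that "300 kcal doses of PA will increase RRV_PA_ more than 150 kcal doses and no PA". Section D tests it with a general linear model that has baseline RRV_PA as a covariate. It names no analysis population.

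**The concern.** An eligibility criterion should be decidable before allocation. This one is not, because it depends on behaviour during the assigned treatment. It can remove people from the 150 and 300 kcal arms, while comparable people allocated to 0 kcal stay in.

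The removal is also unlikely to be neutral. RRV_PA measures how hard a person will work for access to exercise, and the background section says that it predicts usual activity. Someone who repeatedly fails to complete sessions is plausibly someone whose RRV_PA is low or has not risen. If such people leave the exercise arms, those who remain are selected for higher RRV_PA. A difference from control can then appear without any treatment effect. The exercise v no-exercise part of the primary hypothesis would no longer rest on randomisation. Outcome data that were never collected could not be recovered at the analysis stage.

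**Working it through.** **1. Can the criterion act before randomisation?** The procedures run from screening and consent, through three baseline assessment days, to the six-week intervention. No supervised exercise precedes the intervention, so there is no session to miss before allocation. The rule is therefore post-randomisation.

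**2. Which arms can meet it?** The 150 and 300 kcal arms can. The 0 kcal arm has no sessions during the study and no session monitoring, so it cannot.

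**3. Sample size per dose.** Section D plans for SD 8, a difference of 7, alpha 0.05 (taken as two-sided) and 90% power. This needs n = 2 × (1.960 + 1.282)² × 8² / 7² = 27.5, that is 28 per dose. Table 1 has 15 per sex-by-dose cell, so 30 per dose, with power of about 92%. The planned figure is reproduced on that reading, and 30 per dose is used below.

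**4. Illustrative bias, exercise v 0 kcal.** Two inputs are not in the protocol and are assumed: q, the share removed from an exercise arm (10% to 30%), and ρ, the correlation of the trait behind compliance with week-6 RRV_PA (0.3 to 0.5). If the lowest q of a normal trait is removed, the mean outcome of those who remain shifts by

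bias = SD × ρ × φ(z_q) / (1 − q).

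The factor φ(z_q)/(1 − q) is 0.195, 0.350 and 0.497 for q = 10%, 20% and 30%. With no true effect and no replacement, SE = 8 × √(1/(30(1 − q)) + 1/30), and type I error ≈ P(|Z + bias/SE| > 1.96).

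| q | ρ | Bias (units) | % of 7 | SE | Type I error |
|---|---|---|---|---|---|
| 10% | 0.3 | 0.47 | 7% | 2.12 | 6% |
| 10% | 0.5 | 0.78 | 11% | 2.12 | 7% |
| 20% | 0.3 | 0.84 | 12% | 2.19 | 7% |
| 20% | 0.5 | 1.40 | 20% | 2.19 | 10% |
| 30% | 0.3 | 1.19 | 17% | 2.28 | 8% |
| 30% | 0.5 | 1.99 | 28% | 2.28 | 14% |

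Simulating the two-sample t-test gives 5.0% to 14.1% over the same grid. With ρ = 0 there is no bias.

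**5. 300 v 150 kcal.** The bias is the difference between the two arms' shifts, 8 × ρ × (difference in factors).

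- Equal removal (20% and 20%): zero.
- 20% at 300 kcal and 10% at 150 kcal: 8 × ρ × 0.155 = 0.37 to 0.62.
- 30% and 10%: 8 × ρ × 0.302 = 0.72 to 1.21.
- 10% and 20%: the sign reverses, −0.37 to −0.62.

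**6. Effect of the baseline covariate.** Suppose the trait correlates equally with baseline and week-6 RRV_PA, and the baseline to week-6 slope is 0.5 to 0.7 (also assumed). Adjustment then multiplies the bias by about 1 − slope, that is 0.3 to 0.5. The range in step 4 becomes about 0.47 × 0.3 = 0.1 to 1.99 × 0.5 = 1.0 units. If non-compliance reflects a poor response during treatment rather than low baseline motivation, the covariate corrects less.

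**7. Power.** Removing 10%, 20% or 30% from each exercise arm leaves 27, 24 or 21 per dose. Power for 300 v 150 kcal falls from about 92% to 89.5%, 85.8% or 80.9%.

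**The case against.** The protocol lists the item but does not say what follows from it. It does not state that a non-compliant participant misses the week-6 and week-10 tests or leaves the analysis, and an analysis plan that is not shown could keep such people in. This stands as a limit on certainty: the documents support saying that the comparison can be expected to be biased, not that it is biased. It does not remove the point. Exclusion from the study is the natural reading of an exclusion criterion, and an analysis plan cannot restore assessments that were never made.

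Four stronger readings are tempting but not supported.

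- **The powered comparison is biased towards exercise.** Section D powers 300 v 150 kcal, and both arms face the rule. Bias there needs unequal removal.
- **Removal will be heaviest at 300 kcal.** This is plausible, because each session asks for twice the expenditure. But no compliance figures by dose are given, both arms have three sessions a week, and intensity and duration are left free.
- **Non-compliers will be replaced by compliers.** The sentence "Recruitment will continue until the study needs are met" stands in a paragraph on advertising, and nothing mentions replacing randomised participants.
- **False-positive rates are very high.** A rate of about 27% needs 30% removal, a correlation of 0.7, full replacement and no baseline covariate, all together: bias 8 × 0.7 × 0.497 = 2.8, SE 8 × √(2/30) = 2.07.

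The baseline covariate is a fair counterweight, and step 6 of the working allows for it.

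**Conclusion.** The point holds as a fault in a stated rule. The criterion is a post-randomisation exclusion, it can be met in the exercise arms only, and it is plausibly related to RRV_PA. Exercise v 0 kcal is exposed whenever that relation exists; 300 v 150 kcal is exposed only if the doses lose different shares.

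The direction is the expected one, but the size is not known. The illustrated spurious difference of about 0.5 to 2.0 units, and about 0.1 to 1.0 after baseline adjustment, rests on assumed removal rates and correlations. It is modest beside the planned difference of 7. The change is still warranted, because the rule weakens the randomised basis of part of the primary hypothesis and the lost data cannot be recovered later.

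**What to change.** Delete the non-compliance item from the exclusion criteria in C. Methods, i. Participants and screening. In C. Methods or section D, state that:

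- every randomised participant is assessed at weeks 6 and 10 whatever their attendance;
- no one is replaced on grounds of non-compliance;
- the primary analysis keeps each participant in the arm to which they were randomised;
- session compliance and any per-protocol analysis are reported as supportive only.

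This concerns follow-up and analysis and changes no exercise dose. The cost is a one-line deletion, a few added sentences, and the effort of bringing non-attenders back for testing. The observed effect may be somewhat smaller because non-compliers stay in.

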**iii. Procedures**:

Visit One: Screening and Consent

Participants will be recruited by Grand Forks Human Nutrition Research Center (GFHNRC) staff using Survey Monkey. We will leverage our partnership with Choice Health and Fitness to utilize their electronic entry records and send recruitment materials to those fitness club members who attend Choice Fitness 2 or fewer visits per week and otherwise seem to meet our other entry criteria. Various other media will be used to advertise the study. This may include brochures, print media such as the Grand Forks Herald, Dakota Student, Exponent, and Tidbits, television and radio such as the UND television and radio stations. Internet advertisements including University Research Newsletter, University Letter, HEALTHY-UND Listserv, and Work Well Newsletter may be utilized. Recruitment efforts may also include posting flyers around the Greater Grand Forks area and surrounding communities, promoting the study at expos and trade shows, and providing information on the GFHNRC website. Recruitment will continue until the study needs are met. A sample advertisement is attached (APPENDIX 1 a/b). Subjects may apply to join the study by completing the on-line application on Survey Monkey (APPENDIX 2). Eligible applicants will be invited to an information/screening appointment at the GFHNRC or CHF. During this initial visit, subjects will be informed about the study and have any questions answered. If deemed eligible and the subject desire to participate, they will be asked to provide written informed consent (APPENDIX 3). After signing the consent, subjects will fill out a demographic form (APPENDIX 4), a medical history form (APPENDIX 5), and be measured for anthropometrics. Subjects will also be provided a SenseWear device to wear for the following week to monitor free-living energy expenditure and physical activity. Questionnaires including The Preference for and Tolerance of the Intensity of Exercise Questionnaire (PRETIE-Q) (Appendix 6) [[30](#_ENREF_30), [31](#_ENREF_31)], the Discomfort Intolerance Scale [[32](#_ENREF_32)] (Appendix 7), Social norms [[33](#_ENREF_33)], Social Support and Exercise Survey (APPENDIX 8) [[34](#_ENREF_34)], the Exercise Self-Efficacy Scale (EXSE, Appendix 9) [[35](#_ENREF_35)] and the Exercise Confidence Survey (APPENDIX 10), Psychological needs satisfaction (PNSE) (APPENDIX 11), and the Behavioral Regulation in Exercise questionnaire (BREQ-3) (APPENDIX 12) will be completed by the subject at this time. The first of four dietary recalls will be completed and the subject will be scheduled for their three baseline visits at (CHF).

Baseline Assessment Day 1 (CHF)

Subjects will arrive at CHF at least 2 hrs after eating to complete the physical activity reinforcement task (RRV_PA_). Participants will first rate their liking of the PA and sedentary alternatives (Appendix 13). The highest rated PA and sedentary alternatives will be provided as alternatives for the RRV testing session. Additionally, treatment expectations of the study will be assessed with the Stanford Expectations of Treatment Scale (SETS) [[36](#_ENREF_36)] tailored for the current study (APPENDIX 14). The SETS tool assesses expectancy effects to be co-varied for in the statistical analyses. Participants will complete a dietary recall.

Baseline Assessment Day 2 (CHF)

Subjects will arrive at CHF at least 2 hrs after eating to complete body composition and aerobic fitness tests. Body composition will be determined by DXA and submaximal fitness tests will be completed on a motorized treadmill. Participants will complete a dietary recall.

Baseline Assessment Day 3 (CHF)

Subjects will arrive at CHF at least 2 hrs after eating to complete an affect-during-exercise treadmill test. Affect will be measured using single item scales including the Feeling scale (APPENDIX 15) to measure affective valence [[37](#_ENREF_37)], Felt Arousal Scale (APPENDIX 16) to measure perceived activation [[38](#_ENREF_38)], and Borg’s Rating of Perceived Exertion scale (APPENDIX 17) to measure perceived effort [[39](#_ENREF_39)]. Participants will also complete muscular pain scales (APPENDIX 18) during exercise and the multi-item Activation-Deactivation Adjective Check-list (APPENDIX 19) pre-post exercise as a measure of energetic arousal and tense arousal [[40](#_ENREF_40)]. Affect, perceived exertion, arousal, and muscular pain will be measured using single item scales at rest, the last 30 s of a 3 min warm-up (40% < ventilatory threshold (VT)), the last 30 s of every 3 min during 12 min of exercise at an intensity 20% < VT, the last 30 s of every 3 min during 12 min of exercise at an intensity 10-15% > VT, at the end of a 5 min cool down (at an exercise intensity of 20% < VT) and after 10 minutes of rest. Participants will complete the multi-item Activation Deactivation Adjective Check List (APPENDIX 17) before and after completing the exercise. During rest and exercise, heart rate will be measured via telemetry from a chest band (Polar Electro Inc., Lake Success, NY). Beat-to-beat blood pressure, stroke volume, total peripheral resistance, cardiac output, and pulse rate variability will be monitored using a Finometer PRO (Finapres Medical Systems, Amsterdam). Participants will complete a dietary recall and be scheduled for initiation of the 6-week intervention period.

6-Week Intervention The treatment is based on meeting the prescribed kcal expenditure as measured using the SenseWear device (described below) three times per week. The intensity, duration, and interval/ constant load nature of physical activity will not be prescribed. For approximately the first six sessions, a research assistant will be present to provide instruction on the use of the stationary exercise machines and will monitor each session for attaining the energy expenditure goal of either 150 kcal or 300 kcal. The study-related exercise will be a circumscribed and intentional bout recorded by the participant in a log book. Compliance regarding the energy expenditure of each physical activity session will be monitored by the subject and staff using an activity monitor. A research assistant will meet with the subject each week at the fitness center to download and review the activity monitor wear log (APPENDIX 20) and activity monitor data with the volunteer. Volunteers will be given feedback if the exercise bout cannot be readily identified from the activity monitor or if the bout did not meet the energy expenditure criteria. To promote external validity and minimize seasonal/weather effects, treatment sessions will occur at the fitness center. Subjects in the 0 kcal group will wear the physical activity monitor only during assessment periods. No instruction will be provided regarding dietary intake as spontaneous change in dietary intake is an outcome measure.

Week-6 Assessments (Post)

At the conclusion of the intervention, participants will follow the testing schedule outlined for the baseline assessments. Additionally, the Perceived Autonomy support questionnaire will be administered (APPENDIX 21) and subjects will be issued an activity monitor to wear for the following week and will return to CHF to return the device.

Week 10 Assessments

After four weeks of no-contact with the study investigators, subjects will follow the testing schedule outlined for the baseline assessments except they will not complete a body composition test. Subjects will be issued an activity monitor to wear for the following week and will return to CHF to return the device.

**iv. Measures**: Gender, baseline age, and baseline values of outcomes will be tested as moderators of change in RRV of physical activity (**Table 2**).

